## Evaluation

The evaluation will based on the program **theory**, both processes and outcomes being assessed (see figure 3).

**The intervention process** will be assessed in all the 12 health facilities using structured observations of health facilities activities, regular meeting in the health facilities, interview of caregiver and health workers, and a cross-sectional survey.

**Figure 3:** The programme theory

**Inputs**

Staff

Equipment

**Supportive supervision**

**Improving functioning**

-Training Health care providers in IMCI

- Reorganizing GMP activities

- Introducing home visits for sick and severe malnourished children

-Introducing an integrated accreditation scheme for health facilities

**Improving structure**

- Production of a Ready to Use Therapeutic Food

- Adapt management of severe malnutrition cases to local conditions

- Integrated psychosocial stimulation

**Outputs**

Health workers communication and management skills in nutrition improved

Health providers knowledge about nutrition counseling and practices improved

Caretakers knowledge about basic nutrition counseling and complementary feeding practices improved

Caretakers satisfaction with health care, caretakers compliance with recommended feeding practices

Effectiveness of acute malnutrition case management

Effectiveness of psychosocial stimulation activities

**Outcomes to measure**

Child morbidity and mortaliry improved

Child dietary intake improved

Improved children nutritional status

Improved child psychomotor development.

**Improving communication**

-Training healthcare providers in patient-centreedness and communication

**The intervention component**

**The intervention impact on health facilities functioning, child health and nutrition status:**

*Primary outcomes:*

- Child weight and height at 6 and 12 months

-rate of acute malnutrition

*Secondary outcomes*:

-Health provider’s knowledge about nutrition counseling and practices

-Caretakers knowledge about basic nutrition counseling, and breastfeeding and complementary feeding practices

- Caretakers satisfaction with health care

-Implementation of recommended feeding practices

-Child dietary intake

**Evaluation tools:**

The reference guidelines of the IMCI program evaluation and the modules of assessment of the quality of the nutrition cares developed by HKI will be adapted, and will be used for the assessment of the different components of the intervention .

## Data collection:

Data will be collected by trained field workers who are not involved in the delivery of the intervention:

-Interview through a structured questionnaire before, 3 month after the training of health workers and at the end of the intervention to test their knowledge on child nutrition counselling;

- Direct observation of five sick children consultation, and five preventive consultation with each provider, at the same time (before training, 3 month and 12 after the training) to test health providers’ skills in child health and nutrition management, their practice of communication and attitudes with regard to the children and their parents, the aspects related to the context of the meeting (latency, duration of the consultation…) and the quality of care provided.

- Exit interview with caregivers to measure their satisfaction as regards the services offered (growth promotion Program, curative care, communication and relation between health workers, nutrition counseling, malnutrition cases management), their practical knowledge, aptitudes as regards pregnant woman and the young child feeding practices, adapted care, family planning, etc

- At 3, 9 and 12 months, morbidity, health facilities use, anthropometry assessment, breastfeeding/complementary feeding practices reported on at 24-hour dietary recall and child psychosocial development assessment will be made.

# INTRODUCED CHANGES AND EXPECTED RESULTS:

**The principal changes introduced** will be in the structural dimension of health system:

- The decentralization of severe acute malnutrition case management in the primary health centres,

- The production and introduction of a local Ready to Use Therapeutic Food in the health system.

- At Community level, the families will be indirectly concerned in the detection and the rehabilitation of malnutrition case.

**The expected effects of this intervention are at two levels**:

*1°) On the level of the outputs*: health providers should increase their knowledge on child health and nutrition (knowledge). They should have ability to evaluate child nutritional state, to analyze the causes and to identify the adequate initiatives. They should be more effective in the child growth promotion activities, child illness and malnutrition management. The providers will enhance their skills on communication and nutrition counseling with caregivers; they will be more motivated.

Caretakers will find more satisfaction with health care (sympathy and answers adapted to their waiting). This should lead to an increase in the use of the curative and preventive services, a greater regularity and a larger cover of the services, a better tracking of the cases of malnutrition, a reduction severe acute malnutrition cases, good practices in pregnant woman and young child feeding (suitable (breast feeding, weaning…). For the malnourish children, fast rehabilitation is awaited, at a low cost, with a reduced probability of decline on the level of the family.

2) *On the level of the outcomes*:

More frequent and more appropriate use of health services, and changes in food practices, an improvement of the child development, nutritional and medical state is awaited. This one will be measurable in terms of vaccine cover, improved nutritional indicators and by a reduced morbidity.

# . DATA ANALYSIS:

A double entry by two distinct operators, will be done using the software EPIDATA . The comparison of the two data bases will make it possible to correct the major errors.

After cleaning, a scoring will be established for the various indicators. The quantitative variables will be categorized in discrete variables, some synthetic scores will be built for the variables expressing same dimension, and the analysis will be done on software STATA version 10 in three stages. Linear regression and logistic regression will be used to assess the effect of the intervention on continuous and dichotomic variables, respectively. Mixed models will be used for all analysis to account for the cluster randomization and the repeated measurements at the individual level. Qualitative data will be coded and analyzed in QSR 8.0

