## Population and sample size

This study concerns all the health workers in the primary health facilities of the Houndé district and the children from 0 to 24 months as well as their mother or caretakers. The intervention unit is the health center and the population living in its catchment area, i.e. health centers will be randomized.

For the evaluation as well of the efficiency as of the impact of this intervention, the statistical unit will be consisted the center of health and its population of cover. On the level of each statistical unit, three types of samples will be necessary in comparison with the study populations:

- Health workers

A random sample of one health worker will be made by center.

*Inclusion criteria*: Personnel of health having at least one year of activity in the center.

Caregivers

Insofar as several outcomes used to compare the two groups of mother, the principal outcome used to compare the two groups, will be the proportion of caregivers having a good score of Knowledge on adequate breastfeeding and complementary feeding practices.

Several hypothesis have been considered to estimate the sample size. The reference method for the sample size calculation is the paper of Hayes et al for cluster design; we used equation N°4 of this paper

C=number of pairs=6 in our case Km = intracluster correlation coefficient; in the case of paired groups, 0, 25 is used as conservatory value.

= proportion of caregivers with a good score of Knowledge in the control group

= proportion of caregivers with a good score of Knowledge in the intervention group

n=sample size by cluster

The value of C being known in our case, we deduced from this equation, the values of n, according to several assumptions on the rate of caregivers with good knowledge and practices on breastfeeding and complementary feeding and according to two levels of power 1-β=0,80 or 0,90. This is shown in the table below.

**Estimate of the number of caregivers** necessary to compare the two groups

| = 0,25 | α=0,05  1-β=0,80 | α=0,05  1-β=0,90 |
| --- | --- | --- |
|  | n=15 | n=50 |
|  | n=33 | n=95 |
|  | n=11 | 20 |

By taking a maximum power, a sample of 95 women per cluster will be necessary, which is 1140 women in total.

*Inclusion criteria*: all women of childbearing age having a child into care from 0 to 59 months and living in the health center catchment area for at least one year at the time of the survey.

Children from 0 to 24 months

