Taking into account the duration of the intervention a notable change on the child nutritional status could be measured at the level of wasting; which is relevant to measure in children 0 to 24 months. The primary outcome, to compare the two groups will be the proportion of wasted children that is to say the proportion of children with weight for height Z score ≤ -2. According to the baseline data, this proportion was 16.4 on average in the district. The same equation cited above was used to estimate the number of required children. We considered the hypothesis that, after the intervention, the proportion of wasted children would decrease from 16.4% to 10% in the intervention area. Considering two levels of power the numbers of required children is summarized in the table below.

Table IV: Estimate of the number of children necessary to compare the two groups

| = 0,25 | α=0,05  1-β=0,80 | α=0,05  1-β=0,90 |
| --- | --- | --- |
|  | n=180 | n=650 |

We also considered other values of:

| = 0,20 | α=0,05  1-β=0,80 | α=0,05  1-β=0,90 |
| --- | --- | --- |
|  | n=115 | n=200 |

| = 0,30 | α=0,05  1-β=0,80 | α=0,05  1-β=0,90 |
| --- | --- | --- |
|  | n=800 | n=5000 |

We finally kept our first hypothesis with = 0.25, 1-β = 0.80 which gives n = 180 (180 children per cluster).

I*nclusion criteria*: all children 0 to 24 months whose parents residing in the health center catchment area for at least one year at the time of the survey.

The selection of women and children will be in population and randomly. In contrast, the number of children required (180 by cluster) being greater than the number of women (95 per cluster), and to be more operational, we will choose to include in the study women of childbearing age with at least a child under 24 months. This will allow us to select our two populations at the same time.

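### The analysis section turns all quantitative variables into categories before analysis, which conflicts with its own linear regression and, read literally, would cut the continuous primary outcome into classes at unstated points

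*Protocol*

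**What the plan says.** The Data Analysis section describes data preparation and modelling in a few sentences. After double entry and cleaning, indicators are scored. Then comes the rule "The quantitative variables will be categorized in discrete variables". The same sentence adds that "some synthetic scores will be built for the variables expressing same dimension" and names the software and a three-stage analysis. The next sentence reads: "Linear regression and logistic regression will be used to assess the effect of the intervention on continuous and dichotomic variables, respectively". Mixed models are then specified for all analyses, to allow for clustering and repeated measurements.

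Under Evaluation, the primary outcomes are "Child weight and height at 6 and 12 months" and, separately, the rate of acute malnutrition. Secondary outcomes include provider and caretaker knowledge, caretaker satisfaction and child dietary intake.

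The Population and sample size section defines two endpoints as proportions. Wasting is "the proportion of children with weight for height Z score ≤ -2". The caregiver endpoint is "the proportion of caregivers having a good score of Knowledge on adequate breastfeeding and complementary feeding practices", with no threshold stated for a good score.

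**The concern.** The categorisation rule covers the quantitative variables as a class. It sets none aside, and it is placed before the modelling step. The next sentence needs continuous variables to exist at that step. An analyst following the first sentence strictly has no measured variable left for the second, except perhaps the synthetic scores, whose scale is not described.

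The conflict matters most for weight and height. They are a primary outcome and continuous by nature, and the protocol gives no cut-point for either. Grouping them would discard within-centre information and leave the effect estimate dependent on where the class limits fall. With 6 matched pairs, precision is already limited. Dietary intake and the scores are exposed in the same way.

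**Working it through.** **1. Which outcomes the rule touches.**

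| Outcome | Form defined in the protocol | Effect of the categorisation rule |
|---|---|---|
| Weight and height at 6 and 12 months (primary) | Measurements, no cut-point | Conflicts with linear regression |
| Dietary intake, satisfaction, scores (secondary) | No categorical form given in the outcome list | Conflicts, to the extent they are continuous |
| Wasting | Proportion with z-score at or below -2 | None; logistic regression fits |
| Caregiver knowledge, as used for sample size | Proportion with a good score, threshold not given | None as to model; the threshold is open |

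The Data Analysis section names no variables. The table applies its general rule to the outcomes listed elsewhere.

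**2. Information kept within a centre by a single cut.** The protocol states no figure for this, so there is none to reproduce. For a normal variable cut where a proportion p lies below the cut, the efficiency relative to the mean is φ(z)² / [p(1 − p)], where z is the normal quantile of p.

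- Median cut, p = 0.5: 0.3989² / 0.25 = 0.637. This is the best that one cut can do.
- p = 0.164 (baseline wasting): 0.2473² / (0.164 × 0.836) = 0.446.
- p = 0.10: 0.1755² / (0.10 × 0.90) = 0.342.

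More than two classes would lose less. The protocol does not say how many classes are meant.

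**3. Allowing for variation between centres.** Variation between centres is not affected by the cut, so it dilutes the loss. In units of the child-level SD, the variance of a centre's result is 1/n + s² for the mean and 1/(e·n) + s² for the cut. Here e is the efficiency from step 2 and s the between-centre SD. Inputs are n = 180 from the protocol ("1-β = 0.80 which gives n = 180") and s = 0.142 to 0.166. The range for s comes from the protocol's value of 0.25, read as a between-centre coefficient of variation and moved to the z-score scale as 0.25 × p/φ(z):

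- 0.25 × 0.164 / 0.2473 = 0.166
- 0.25 × 0.10 / 0.1755 = 0.142

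Both the reading of 0.25 and its use for weight or height are assumptions.

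- Median cut, s = 0.166: (0.00556 + 0.02756) / (0.00872 + 0.02756) = 0.91.
- Median cut, s = 0.142: (0.00556 + 0.02016) / (0.00872 + 0.02016) = 0.89.
- Cut at 16.4%, s = 0.166: 0.03311 / (0.01246 + 0.02756) = 0.83.
- Cut at 16.4%, s = 0.142: 0.02572 / (0.01246 + 0.02016) = 0.79.
- With no between-centre variation, the figures of step 2 apply unchanged.

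**4. A power comparison that does not measure this problem.** The protocol supposes that "the proportion of wasted children would decrease from 16.4% to 10% in the intervention area". On a normal scale this is a shift of −0.978 − (−1.282) = 0.303 SD, if every child shifts equally. Take a pair-matched formula with 6 pairs (6 − 2 = 4 as multiplier), n = 180, two-sided α = 0.05 and the between-centre values above.

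- Proportion: variance (0.1371 + 0.0900)/180 + 0.0625 × (0.0269 + 0.0100) = 0.00357. Then √(4 × 0.064² / 0.00357) = 2.14, and Φ(2.14 − 1.96) gives power of about 57%.
- Mean z-score: variance 2/180 + 0.166² + 0.142² ≈ 0.0589. Then √(4 × 0.303² / 0.0589) = 2.50, and power is about 71%.
- The two are equal when the mean shift is 0.064 × √(0.0589 / 0.00357) = 0.26 SD. At 0.20 SD the mean has about 38% power, and at 0.10 SD about 13%.

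**The case against.** The strongest reply is that the two sentences can be read together. The categorisation clause sits among data-preparation steps, and linear regression would have no purpose if nothing stayed continuous. On that reading, some indicators are grouped for presentation or for proportion endpoints, and continuous outcomes are still modelled as such. This reading is possible, and it rules out a claim that means will certainly never be compared; that follows only from the literal reading. But the text does not state the lenient reading, and the clause as written has no limit.

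A second reply is that the final form of each variable, and its cut-points, can be left to a statistical analysis plan. That would answer a complaint about missing detail. It does not answer a stated general rule that conflicts with the sentence after it, because a later plan could honour only one of the two.

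Three stronger inferences are tempting and not supported:

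- That cut-points will be picked after seeing results by arm. The protocol gives no cut-points for weight or height, but it says nothing about when they would be chosen.
- That analysing wasting or good knowledge as a proportion is itself an error. Both are defined as proportions in the sample size section, and logistic regression suits them.
- That the rule costs the trial the gap between 71% and 57% power. That contrast sets mean weight-for-height z-score against the wasting proportion, an endpoint that stays whatever happens to the clause. It also needs a uniform shift and reverses below about 0.26 SD. Reversal is plausible, since parts of the intervention are aimed at children who are already malnourished or not gaining weight.

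**Conclusion.** The point stands as an internal conflict with a real but moderate cost. An unqualified categorisation rule is set beside linear regression for continuous variables, and on its plain wording it reaches the primary outcome of weight and height. A single cut would keep at most about 0.64 of the within-centre information. Counting between-centre variation as in step 3, overall efficiency is about 0.89 to 0.91 for a median cut and 0.79 to 0.83 for a cut at the 16.4% point.

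These figures assume a normal variable, a pure shift in location, two classes, 180 children per centre, and a between-centre spread borrowed from the wasting calculation. They show the kind of loss involved and are not estimates for weight or height themselves. The textual conflict does not depend on them. The wasting analysis is unaffected. The protocol should be corrected because the rule brings no benefit and leaves the form of a primary analysis unsettled.

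**What to change.** Replace only the categorisation clause in the Data Analysis section. Keep the synthetic scores, the software and the three-stage structure that share its sentence. The replacement should say:

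- Weight, height and their z-scores, dietary measures and scores are analysed as continuous outcomes in the linear mixed models already planned.
- Categories are used only for outcomes that the protocol defines as proportions: wasting at a weight-for-height z-score of -2, and a good knowledge score with its threshold fixed in advance.

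Mean weight-for-height z-score may be reported in support of the wasting result. This is optional, and no gain in power should be claimed for it without stating the uniform-shift assumption and the reversal below about 0.26 SD.

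The change needs no extra children, data or fieldwork. Its cost is a wording amendment and a decision, before analysis, on the knowledge threshold.

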## Study design

The intervention will be evaluated by a pair-matched, cluster-randomized controlled trial . Health facilities, together with the population living in their catchment area, will be matched by pair on the basis of accessibility criteria (distance to the district hospital), functioning criteria (number and profile of health workers, measles vaccine coverage, attendance rates of the growth monitoring programme, utilization rates of health facilities) and population characteristics (households socioeconomic indicators, child morbidity, rates of child wasting and stunting). Scoring of all health facilities will be based on the baseline data, and such score will be used to pair health facilities. Within each pair, one health facility will be randomly allocated the intervention, the other one serving as a comparator.

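### The analysis section does not carry the six matched pairs on which the trial is randomised and sized; it should state a pair-based primary comparison on 5 degrees of freedom

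*Protocol*

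**What the plan says.** **Design.** The Study design section states that "The intervention will be evaluated by a pair-matched, cluster-randomized controlled trial". Centres are paired on a score built from accessibility, functioning and population criteria, including baseline wasting and stunting. Then: "Within each pair, one health facility will be randomly allocated the intervention, the other one serving as a comparator".

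**Sample size.** The Population and sample size section uses a published equation for cluster designs with "C=number of pairs=6 in our case", and sets the between-cluster term on the basis that "in the case of paired groups, 0, 25 is used as conservatory value". The same equation is applied to wasting, on the hypothesis that "the proportion of wasted children would decrease from 16.4% to 10% in the intervention area". The choice made is: "We finally kept our first hypothesis with = 0.25, 1-β = 0.80 which gives n = 180" per cluster. The Evaluation section confirms the number of clusters: the intervention process "will be assessed in all the 12 health facilities".

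**Analysis.** The Data analysis section names linear regression for continuous outcomes and logistic regression for binary ones, in STATA 10, and adds: "Mixed models will be used for all analysis to account for the cluster randomization and the repeated measurements at the individual level". It does not mention pairs. It also names no estimation method (ML or REML), test statistic, reference distribution or degrees of freedom.

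**The concern.** The pair is the block within which allocation takes place, and the sample size relies on it. The analysis section covers all analyses and lists the sources of dependence it will handle: the cluster and the repeated measurement on a child. The pair is not on the list. Read as written, the analysis does not match the design or the calculation that sized the trial.

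At stake are the p-value and confidence interval for the primary comparison. Two mechanisms act in opposite directions and should be kept apart:

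- **Omitting the pairs.** Centres in the same arm come from different pairs, so the between-centre variance within an arm contains the between-pair variation that matching was meant to remove. The standard error is then too large and the test conservative.
- **The reference distribution.** However many children are measured, 12 centres inform the treatment contrast. A normal or chi-squared reference is too liberal for 12 clusters when matching does little.

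**Working it through.** **Inputs.** Six pairs and 12 centres; alpha 0.05 (two-sided assumed, since the protocol does not say); 180 children per cluster; 16.4% against 10% wasted; between-cluster term 0.25. The within-pair correlation of the centre-level outcome, rho, is not in the protocol and is shown as a range.

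**1. The plan's own figure.** The equation is not visible in the text. Assuming the usual matched-pair form,

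c = a + (z_alpha + z_beta)² × [p0(1−p0)/n + p1(1−p1)/n + k²(p0² + p1²)] / (p0 − p1)²,

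with c = 6, k = 0.25 and 80% power, n per cluster is:

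| | a = 0 | a = 1 | a = 2 |
|---|---|---|---|
| two-sided | 275 | 749 | none finite |
| one-sided | 136 | 226 | 660 |

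The stated 180 is not reproduced by any of these. That is a separate matter, but it bears on the power figures in step 4.

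**2. Effect of omitting the pairs.** Let σ² be the total variance of a centre mean. The difference between arm means has true variance 2σ²(1 − rho)/6, while an analysis without pairs estimates 2σ²/6. The standard error is too large by 1/√(1 − rho): 1/√0.75 = 1.15 at rho 0.25, and 1/√0.5 = 1.41 at rho 0.5.

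**3. Size of a nominal 5% test.** For 6 against 6 centre means and no matching effect (rho 0), the tails are exact:

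- z reference, unbiased (REML) variance: P(|t10| > 1.96) = 7.8%.
- z reference, ML variance: P(|t10| > 1.96 × √(10/12)) = 10.4%.

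For the other values of rho, cluster means were simulated (200,000 per setting). The two logistic rows come from 4,000 simulated trials per setting (12 × 180 children, 16.4% wasted, between-cluster coefficient of variation 0.25, random-intercept logistic model fitted by ML without pairs).

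| Analysis | rho 0 | rho 0.25 | rho 0.5 |
|---|---|---|---|
| No pairs, t on 10 df | 5.0% | 2.9% | 1.2–1.3% |
| No pairs, REML Wald z | 7.8% | 4.8% | 2.3% |
| No pairs, ML Wald z | 10.4% | 6.7% | 3.4% |
| Logistic mixed model, Wald z | 10.7% | 7.1% | 4.6% |
| Logistic mixed model, likelihood ratio | 8.2% | 5.5% | 3.7% |
| Paired t on 5 df | 5.0% | 5.0% | 5.0% |

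Adding pairs while keeping a z reference does not help: P(|t5| > 1.96) = 10.7% with an unbiased variance. With fixed pair effects under ML it is P(|t5| > 1.96 × √(5/12)) = 26%.

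**4. Power on the planning inputs, reading 0.25 as the within-pair coefficient of variation.**

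- Binomial part: (0.164 × 0.836 + 0.10 × 0.90)/180 = 0.00126.
- Between-cluster part: 0.25² × (0.164² + 0.10²) = 0.00231.
- Variance of one pair difference: 0.00357. Standard error of the mean of six: √(0.00357/6) = 0.0244.
- Standardised effect: 0.064/0.0244 = 2.62.
- Power with a z reference: Φ(2.62 − 1.96) = about 75%. With a paired t on 5 df (critical value 2.571), from the non-central t: about 56%.

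**The case against.** **The protocol does not prescribe a large-sample test.** This stands. The section names neither ML nor REML and gives no reference distribution, and such detail is commonly left to a statistical analysis plan, which may exist. The missing small-sample correction is therefore not in itself an error. A reader might infer that the planned test runs at about 10%. The document does not support that: the figure needs ML estimation, a Wald z test and matching that explains nothing, all together.

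**Omitting pairs does not inflate the false-positive rate.** This also stands. At rho 0 the unpaired t on 10 df gives 5.0%, so nothing is lost in size. The inflation comes entirely from an assumed large-sample reference. A reader might link the two as cause and effect, but omitting pairs acts in the opposite direction.

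**A mixed model can hold a pair level, and the randomisation being accounted for is itself pair-matched.** This stands in part. The text does not exclude a pair term. But it says what the models are for, applies them to all analyses, and names clustering and repeated measures only. It should not be left to inference whether the blocking used in randomisation and sizing enters the model.

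**The paired test costs power, and the unpaired t on 10 df is an alternative.** True: at the same standard error the 10-df test has about 66% power. The same standard error applies only when matching achieves nothing. When matching works, the unpaired test becomes conservative, and matching partly on baseline wasting is meant to make it work. The 75% with a z reference is not a fair rival either, since a paired z test has a size of 10.7%.

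**Conclusion.** The point holds as a mismatch between sections: pairs are used in randomisation and sample size but are not carried into the stated analysis. Its size depends on two things the protocol does not give, the within-pair correlation and the reference distribution.

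- With a t reference on 10 df and no pairs, size falls from 5.0% at rho 0 to about 2.9% at 0.25 and 1.2–1.3% at 0.5. The precision that matching was meant to buy is lost.
- With large-sample tests, if they were used, size is about 8–11% at rho 0 and falls below 5% as matching improves (2.3–4.6% at rho 0.5).
- Of the analyses checked, only the paired t on 5 df holds about 5% at every rho.

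It does not follow that the primary p-value will be anti-conservative. Its direction cannot be told from the protocol, which is why the analysis should be fixed before outcome data are seen by arm. The power figures rest on reading 0.25 as a within-pair coefficient of variation and on an assumed form of the equation. The protocol calls this quantity an intracluster correlation coefficient, and the equation is not visible.

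**What to change.** Amend the Data analysis section as follows.

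- **Primary comparison of wasting.** Compute each centre's log-odds or prevalence of wasting (state which), take the six within-pair differences, and report their mean with a paired t-test and 95% confidence interval on 5 degrees of freedom. A mixed model with a pair effect and a 5-df t reference is an acceptable equivalent.
- **Time point.** Apply this at whichever time point the protocol fixes for wasting. The Evaluation section gives none for acute malnutrition, and the Data collection section lists assessments at 3, 9 and 12 months.
- **Continuous outcomes.** Use the same rule.
- **Present mixed models.** Keep them as supportive analyses.
- **What to avoid.** Do not simply add pair fixed effects to an ML model with a z reference; size would be about 26%. The pair term and its degrees of freedom must be stated together.

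**Cost.** No change to design or data collection, but more than wording. The interval multiplier rises from 1.96 to 2.57, and on the planning inputs power is about 56% rather than the stated 80%. Restate the power with the chosen analysis, show the equation, and say whether 0.25 is a coefficient of variation or a correlation.
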